#### Clinician intervention

- At the start of the intervention period, the principal investigators and the Project Manager will present a 15-minute educational session to internal medicine and family medicine PCPs at their monthly team meeting at each of the intervention clinics. The presentation will include:
  - A short slide presentation on how deprescribing is one element of optimal medication management for older adults. The presentation will include evidence-based information on what deprescribing is and when and how to consider it. It will also include example situations where deprescribing may be beneficial. The presentation will also provide general information on the study and will include contact information for the study principal investigators and local study staff.
  - We will ask clinicians to complete (on paper) at the meeting a 9-question Prescribers' Perceptions of Medication Discontinuation (PPMD) questionnaire regarding opinions on deprescribing at beginning of presentation.
  - A list of Internal Medicine and Family Medicine clinicians at each of the intervention clinics will be obtained and any providers who missed the initial presentation will be sent a letter of introduction to the study, copy of the Optimize presentation and the PPMD questionnaire, requesting that they complete it and send back to the KPCO Project Manager.
  - Newly hired physicians joining practices will be oriented to the intervention by the KPCO PI and project manager after they complete their initial clinical orientation.
- One-page paper Tip Sheets handed out to providers at monthly meetings. The Tip Sheets contain information on approaches and language to use in specific medication discontinuation situations. Eleven Tip Sheets were developed based on clinician interviews. Example topics include:
  - Limited life expectancy.
  - Potential for harm.
  - Limited evidence for effectiveness.
  - Medications have reached maximum benefit.
- Primary care clinicians will receive notification via an appointment note in the EHR when study materials have been sent to patients with an upcoming appointment.
- At the intervention conclusion, primary care clinicians will be provided a poster that is a colorful

summary of the titles of all Tip Sheets.

### 3.2 Delayed Control Intervention

We plan to conduct the delayed control intervention in the nine clinics that provided usual care during the initial intervention from ~September 2021 through ~February 2022.

### 3.3 Concomitant Interventions

There are no concomitant interventions. All medical care will proceed according to the decisions of the patient, care partner and primary care provider.

## 4 STUDY PROCEDURES

### 4.1 Schedule of Evaluations for initial intervention

| Assessment                                                                     | Identify Eligible Population | Baseline, Enrollment, 2 weeks prior to scheduled visit | 6 months post brochure mailing | 12 months post brochure mailing |
|--------------------------------------------------------------------------------|------------------------------|--------------------------------------------------------|--------------------------------|---------------------------------|
| Inclusion/Exclusion Criteria                                                   | X                            |                                                        |                                |                                 |
| Demographics- age, gender, race, ethnicity                                     | X                            |                                                        |                                |                                 |
| Primary outcomes (Aim 1)                                                       |                              |                                                        |                                |                                 |
| Current Medications                                                            | X                            | X                                                      |                                |                                 |
| Number of Drugs                                                                | X                            | X                                                      | X                              | X                               |
| Percent of individuals with one or more Potentially Inappropriate Medications* | X                            | X                                                      | X                              | X                               |
| Secondary outcomes (Aim 2)                                                     |                              |                                                        |                                |                                 |
| Dose Reductions                                                                |                              |                                                        |                                | X                               |
| rPATD                                                                          |                              | X                                                      |                                |                                 |
| ADE rates                                                                      |                              | X                                                      |                                | X                               |
| ADLs                                                                           |                              | X                                                      |                                | X                               |
| Hospitalization rate*                                                          |                              | X                                                      |                                | X                               |
| Skilled Nursing Facility admission rate                                        | X                            | X                                                      |                                | X                               |
| Mortality*                                                                     |                              |                                                        |                                | X                               |
| PPMD                                                                           | X                            |                                                        |                                |                                 |

\* Hospitalization, and mortality will be assessed every 3 months for safety monitoring, but not as secondary outcomes. Medication list attached at end of protocol.

### 4.2 Description of Evaluations

Study evaluation will focus on primary and secondary quantitative outcomes with initial results focused on primary outcomes.

### 490 Definitions

of assessment variables from Schedule 4.1 above and associated data elements and sources are itemized

below. Unless otherwise mentioned, all data will be extracted from the KPCO Virtual Data Warehouse, a quality controlled, common data model that includes data from multiple KPCO data sources covering the following domains: Enrollment, utilization, pharmacy, tumor registry, demographics, lab results, mortality, vital signs, census data, geocoded demographic data, patient reported outcomes collected in the course of care, problem list diagnoses, and social history.

Inclusion/ exclusion criteria: as previously described. Data elements will include age, diagnosis codes, location of primary care provider, current medications. Chronic diagnoses will be from a list of 86 chronic conditions itemized in the Multiple Chronic Conditions Chartbook (Gerteis J, et al.). We have developed a method of counting chronic medications that utilizes the Generic Product Index (GPI) in a manner similar to prior work using the WHO Anatomic Therapeutic Chemical index A. Study experts ([name], [name], [name], [name], [name]) created a consensus-based list of GPI categories to be included in estimating the criterion of 5 or more chronic medications (this list excludes drug classes unlikely to be used as chronic medications, such as vaccines and anesthetics).

Demographics: age, gender, self-reported race/ethnicity from the EHR, census-based socioeconomic status.

Diagnoses: ICD-9 (historical) and ICD-10 codes will be used to identify diagnoses from visit billing codes, hospital and emergency department claims, and problem list diagnoses.

Current chronic medications: Total number of chronic medications on the date of study eligibility. Chronic medication use is defined as any medication for which the patient had at least a 28-day supply on the baseline eligibility date. We selected a 28-day supply (rather than a supply for a longer time period) because opioid medications are often dispensed in 28-day supplies. All current medications exclude the following domains identified by 2-digit GPI codes: Vaccines, Toxoids, Allergenic extracts, Oxytocics, Local anesthetics – parenteral, General anesthetics, Antiseptics and disinfectants, Antidotes, Diagnostic products, Chemicals, and Medical devices.

Primary Outcomes:

Number of drugs: number of chronic medications – see above.

Percent of individuals taking one or more PIMs: chronic medications that are listed as potentially inappropriate for older adults based on the Beers list plus opioid medications.

520 Secondary Outcomes:

521 Dose reductions: Because calculating dose reductions requires analyzing specific targeted medications, we  
522 will assess dose reductions in three selected drug classes. We selected these classes based on the premise  
523 that the medications posed risks of adverse side effects, but that patients, care partners, and clinicians may  
524 be reluctant to discontinue the medications for fear of recurrent symptoms. The three drug classes are  
525 benzodiazepines, opiates, and antipsychotics.

526 Adverse Drug Events: We will examine three types of ADEs that are common causes of emergency service  
527 use among older adults and that may plausibly be expected to decrease in a culture of thoughtful  
528 deprescribing. These are falls; hemorrhagic events; and episodes of hypoglycemia in individuals with  
529 diabetes. All of these outcomes will be calculated from ICD-10 diagnoses using code lists extracted from  
530 the literature and/or previously validated at KPCO. Rates will be calculated for the year prior to baseline  
531 and the year following the initial brochure mailing. Denominators will use person-years to account for  
532 changes in enrollment and deaths.

533 ADLs: Activities of Daily Living are reported by patients/ proxy responders as part of the annual Medicare  
534 Health Risk Assessment (HRA). These data will be available on the subset of patient participants who have  
535 completed the HRA. (Estimated at 45% of the KPCO Medicare beneficiary population.) Data from the most  
536 recent HRA will be used.

537 Hospitalization rate, emergency department visit rate, skilled nursing facility admission rate: Presence/  
538 absence of a one of these admissions over the year prior to baseline and post intervention. (We will  
539 distinguish between temporary and permanent admissions to skilled nursing facilities.)

540 Mortality: Death from any cause during the study period.

541 Additional planned evaluations:

542 Following the intervention, we will explore mechanisms of intervention effectiveness and uptake through  
543 post hoc qualitative interviews with patients, family caregivers, and clinicians; patient and clinician survey  
544 responses; and descriptions of outpatient office visit length. Data and variables include:

rPATD: revised Patients' Attitudes Towards Deprescribing 9-question questionnaire and one question on who completed it. Collected from patients/ care partners as part of the intervention on paper and returned by mail.

PPMD: Physicians Perception of Medication Discontinuation. Collected on paper during the initial portion of the clinician intervention – presentation at clinician team meeting.

Physician specialty: Will be obtained from Colorado Permanente Medical Group data sources.

Time and interval definitions: Enrollment, Baseline, and/or Randomization:

Baseline: The baseline point will be defined as the time at which patients are identified as having an upcoming appointment with their PCP and are mailed the intervention materials. For patients who receive second mailings in advance of a subsequent PCP visit, baseline will remain their first visit but second mailings will be tracked and examined in selected analyses. Baseline for patients in the control clinics will be the date of the first PCP appointment during the initial intervention period. Identical methods will be used to screen control patients for eligibility and identify upcoming visits as described above to ensure comparable identification.

Randomization: Randomization will be at the clinic level and will be stratified by clinic size. (See analytic plan below.)

Follow-up Visits: Data extractions do not depend on follow up visits in this study. Dates for follow up measurements described in the Evaluations Table will be relative to baseline and data will be extracted from the VDW as described above.

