## **2 STUDY DESIGN**

The study will be a pragmatic, cluster randomized trial with randomization at the level of the clinic and a delayed control group. Clinics will be randomized in blocks of two based on the number of eligible patients per clinic.

Primary outcomes will be total number of medications prescribed and percent of individuals with >1 PIMs prescribed at 6- and 12-months following intervention initiation. Outcomes will be measured with pharmacy dispensing data. PIMs will be based on the Beers List additionally including opioid medications.

Secondary outcomes will include rates of selected adverse drug events (falls, bleeding episodes,

hypoglycemic episodes), dose reductions for selected potentially inappropriate medications (benzodiazepines, opioids, antipsychotics), hospital, emergency department and skilled nursing facility utilization, and activities of daily living reported in the Medicare Health Risk Assessment. Secondary outcomes will be examined following primary outcome analyses.

The eligible patient population will be all KP members ages 65 or greater with a diagnosis of ADRD or MCI from either ICD visit codes or documentation on the problem list, plus at least one other chronic condition. Patients must also be taking 5 or more chronic medications and have a PCP in the KPCO Denver-Boulder area. Of this eligible population, those who schedule a visit with their PCP in an intervention clinic during the study period will receive the intervention.

Exclusion criteria: As the pragmatic trial will be based in primary care clinics, individuals residing in long term care facilities, enrolled in hospice care, or receiving home-based primary care services will be excluded.

The clinician population for the study will be all PCPs who care for adult patients at intervention clinics.

The study setting will be 18 primary care clinics in the KPCO Denver-Boulder geographic area.

The intervention duration will be from April 2019 – February 2022. The initial intervention will run 12 months from March 2019 through April 2020. The intervention for the delayed control group will run from ~September 2021 through ~February 2022. Outcomes for the initial intervention group will be measured at 6 months and 12 months.

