### Potentially Harmful or Inappropriate Medications in Patients with Dementia

| Category                | Subcategory     | Generic name              |
|-------------------------|-----------------|---------------------------|
| H2-receptor antagonists |                 | Cimetidine                |
|                         |                 | Famotidine                |
|                         |                 | Nizatidine                |
|                         |                 | Ranitidine                |
| Anticholinergics        | Antidepressants | Desipramine               |
|                         |                 | Nortriptyline             |
|                         |                 | Paroxetine                |
|                         |                 | Amoxapine                 |
|                         |                 | Protriptyline             |
|                         |                 | Trimipramine Maleate      |
|                         | Antiemetic      | Prochlorperazine          |
|                         | Antihistamines  | Meclizine                 |
|                         |                 | Brompheniramine           |
|                         |                 | Carbinoxamine             |
|                         |                 | Chlorphen-PE-PPA-Atropine |
|                         |                 | Chlorpheniramine          |
|                         |                 | Clemastine                |
|                         |                 | Cyproheptadine            |
|                         |                 | Dexbrompheniramine        |
|                         |                 | Dexchlorpheniramine       |
|                         |                 | Diphenhydramine           |
|                         |                 | Doxylamine                |
|                         |                 | Hydroxyzine               |
|                         |                 | Promethazine              |
|                         |                 | Tripolidine               |
|                         | Antimuscarinics | Darifenacin               |
|                         |                 | Fesoterodine              |
|                         |                 | Oxybutynin                |

|  |             |
|--|-------------|
|  | Solifenacin |
|--|-------------|

|                  |                |                              |

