|                  |                | Olanzapine                   |

|                             |  |                        |
|-----------------------------|--|------------------------|
| Antipsychotics              |  | Paliperidone Palmitate |
|                             |  | Perphenazine           |
|                             |  | Pimozide               |
|                             |  | Piperazine             |
|                             |  | Quetiapine             |
|                             |  | Reserpine              |
|                             |  | Risperidone            |
|                             |  | Thiethylperazine       |
|                             |  | Thioridazine           |
|                             |  | Trifluoperazine        |
|                             |  | Zipresidone            |
| Benzodiazepine hypnotics    |  | Estazolam              |
|                             |  | Flurazepam             |
|                             |  | Midazolam              |
|                             |  | Quazepam               |
|                             |  | Temazepam              |
|                             |  | Triazolam              |
| Benzodiazepines             |  | Alprazolam             |
|                             |  | Chlordiazepoxide       |
|                             |  | Clorazepate            |
|                             |  | Diazepam               |
|                             |  | Halazepam              |
|                             |  | Lorazepam              |
|                             |  | Oxazepam               |
|                             |  | Prazepam               |
| Nonbenzodiazepine hypnotics |  | Ergoloid Mesylates     |
|                             |  | Eszopiclone            |
|                             |  | Isoxsuprine            |
|                             |  | Zaleplon               |
|                             |  | Zolpidem               |
| Opioids                     |  | Alfentanil             |
|                             |  | Buprenorphine Patch    |
|                             |  | Butorphanol            |
|                             |  | Codeine                |
|                             |  | Dihydrocodeine         |

|  |  |               |
|--|--|---------------|
|  |  | Hydrocodone   |
|  |  | Hydromorphone |
|  |  | Levomethadyl  |
|  |  | Meperidine    |
|  |  | Methadone     |
|  |  | Morphine      |

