|  |  | Opium         |
|  |  | Oxycodone     |
|  |  | Pentazocine   |
|  |  | Propoxyphene  |
|  |  | Remifentanyl  |
|  |  | Sufentanyl    |
|  |  | Tapentadol    |
|  |  | Tramadol      |

1052  
1053  
1054  
1055  
1056  
1057  
1058  
1059

Reference:  
American Geriatrics Society 2015 Updated Beers Criteria for Potentially Inappropriate Medication Use in Older Adults. *J Am Geriatr Soc*, 63(11), 2227-2246.

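### The PIM primary outcome has two definitions that disagree: the text counts all opioids, while the attached list names only some and leaves clonazepam out of its benzodiazepines

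*Protocol*

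**What the plan says.** Section 2 of the protocol states that "PIMs will be based on the Beers List additionally including opioid medications". The definitions under Section 4.2 say the same of the primary outcome: "chronic medications that are listed as potentially inappropriate for older adults based on the Beers list plus opioid medications". Neither passage names individual drugs.

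In the schedule of Section 4.1 the row "Percent of individuals with one or more Potentially Inappropriate Medications" carries an asterisk. The footnote first deals with safety monitoring of hospitalization and mortality, which share the asterisk, and then adds "Medication list attached at end of protocol". The attachment is headed "Potentially Harmful or Inappropriate Medications in Patients with Dementia", gives generic names by category, and cites "American Geriatrics Society 2015 Updated Beers Criteria for Potentially Inappropriate Medication Use in Older Adults". It is the only drug-level specification of PIMs in the protocol. It has no wording that brings in unnamed members of a category.

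Section 7.2 gives an expected control rate of 35.8% and a detectable intervention rate of 29.0% or less. It does not say which PIM definition produced the 35.8%.

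**The concern.** Two programmers who each follow the protocol faithfully could score this primary outcome differently. One would count every opioid, as Sections 2 and 4.2 say. The other would match dispensings against the attached names and miss some opioids and at least one benzodiazepine.

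The omitted drugs fall within what the intervention addresses. Section 2 describes a Tip Sheet that gives benzodiazepines as an example of drugs that raise the risk of falls, and says the brochure was adapted from a benzodiazepine intervention. Benzodiazepines and opioids are also two of the three classes chosen for the dose-reduction secondary outcome. Under a literal list, stopping clonazepam would not show in the primary outcome, and replacing a listed drug with an omitted one could look like a PIM removed. The count of PIM starts, a secondary outcome in Section 7.4, would inherit the same gap.

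**Working it through.** **1. What the list contains.** Class membership below is general pharmacology; the cited Beers source is not at hand.

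- Benzodiazepines: 6 entries under hypnotics and 8 under benzodiazepines, 14 in all. The entry "Chlordiazepoxide" is followed directly by clorazepate. Clonazepam would fall between them and is in neither category.
- Opioids: 19 entries. Levomethadyl is followed directly by meperidine (no levorphanol), and oxycodone directly by pentazocine (no oxymorphone).
- Anticholinergic antidepressants: 6 entries, from desipramine to "Trimipramine Maleate". Amitriptyline, imipramine and doxepin are absent. These rows are not alphabetical, so position shows nothing.

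The benzodiazepine and opioid gaps lie inside alphabetical runs, away from page breaks, so a row lost in the layout is an unlikely explanation. Absences that fall at a page break are not relied on.

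**2. The two definitions applied to the same patient.** Assume the drug shown is the patient's only candidate PIM.

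| Patient | Text (Sections 2, 4.2) | Attached list, literally |
|---|---|---|
| Takes oxymorphone | PIM | no PIM |
| Oxycodone replaced by oxymorphone | PIM before and after | PIM before, none after |
| Takes clonazepam | depends on the Beers source | no PIM |
| Lorazepam replaced by clonazepam | after the switch, depends on the Beers source | PIM before, none after |
| Stops clonazepam | depends on the Beers source | no change recorded |

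The opioid rows are a contradiction within the protocol. The clonazepam rows show a list that does not cover its own category; whether the text also counts clonazepam cannot be settled from the protocol. In every replacement row the number of chronic medications, the other primary outcome, is unchanged.

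**3. The plan's own figure.** 35.8 − 29.0 = 6.8 points. The protocol gives no alpha, sidedness, target power or ICC for this comparison. Assume alpha 0.05 and carry over the ICC of 0.01 stated for the medication count:

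- mean clinic size m = 3,671/18 ≈ 204
- design effect = 1 + (204 − 1) × 0.01 = 3.03
- effective n per arm = (3,671/2)/3.03 ≈ 606
- power: 71.6% two-sided, 81.2% one-sided

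Two-sided power is 79.2% at ICC 0.0075 and 87.4% at ICC 0.005. A target near 80% is therefore reachable under unstated inputs, and the 29.0% is neither confirmed nor disputed here.

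**4. Scale of a differential error.** Let s be the share of PIM users in the intervention arm, in excess of control, whose only listed PIM is replaced by an omitted drug of the same class. If 35.8% was obtained from the list, the spurious fall is 35.8 × s points. The values of s are assumptions.

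| s | spurious fall (points) |
|---|---|
| 1% | 0.36 |
| 2% | 0.72 |
| 5% | 1.79 |
| 10% | 3.58 |

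The whole planned difference would need s = 6.8/35.8 = 19.0%.

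**The case against.** The strongest reply is that the list need not govern. The footnote only says that a list is attached, while both defining passages rest on the Beers list and opioid medications. Under those passages oxymorphone and levorphanol count, and moving from oxycodone to oxymorphone removes nothing. That is correct, and it is why the point is a conflict between passages and not a settled scoring error. It does not remove the conflict: the asterisk links the primary outcome to the list, and no order of precedence is given.

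A second reply is that the antidepressant omissions may be right. The list has no tricyclic category, only an anticholinergic antidepressant one that also includes paroxetine, and the Beers source cannot be consulted here. This stands. Those three drugs are an item to check and nothing more.

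A third reply is that code lists belong in the analysis plan or the programming specification. In general they do. Here the protocol attached a list of named drugs to a primary outcome, and that list disagrees with the protocol's own text.

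A reader might go further and infer that clinicians will respond by substituting within a class, more so in the intervention arm, so that the trial will report a false effect. The documents do not support this. Section 3.3 leaves care to patient, care partner and clinician, which permits switching but gives no rate. The materials concern discontinuation, not replacement.

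**Conclusion.** The PIM primary outcome is specified in two ways that give different answers for some patients, and the protocol does not say which applies. This is firm for opioids, where the text is unlimited and the list is partial. For clonazepam, the list is incomplete within its own benzodiazepine categories. For amitriptyline, imipramine and doxepin, the question is open until the cited source is checked.

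The consequence is conditional. It requires that the list be programmed literally and, for a switch, that the patient have no other listed PIM. Omissions that act alike in both arms reduce sensitivity and do not favour either arm. A distortion of the comparison requires a difference between arms, for which there is no figure; the values in step 4 show scale only. Nor can it be said that true PIM prevalence exceeds 35.8%, since the protocol gives neither the definition behind that rate nor the number of patients who take only omitted drugs. The case for acting is that a primary outcome is ambiguous and the repair is cheap.

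**What to change.** - Reconcile the attachment with Sections 2 and 4.2, and state which governs scoring.
- Define at least the opioid and benzodiazepine classes by complete GPI codes, including benzodiazepines filed under other headings. Section 4.2 already uses GPI to count chronic medications.
- Check the remaining categories, including the anticholinergic antidepressants, against the cited Beers source. Where a drug is left out on purpose, say so.
- Freeze the code list before any outcome data by arm are seen, and apply it identically in both arms at baseline, 6 months and 12 months. Use the same list for PIM starts in Section 7.4.
- Re-run the expected control rate on the November 2018 cohort used for the power estimates. If it changes, restate the 35.8% and the 29.0%.

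The cost is a revised code list, one re-run of the prevalence and possibly restated power figures. No new data are needed.
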